**Research Protocol: Recovery from critical coronavirus infection**

**I Background**

Long-term survival after intensive care has risen to an important position in the field's research in recent years. It takes a long time for a patient to recover from a critical illness, and the risk of death for those who leave the hospital alive is elevated for a long time. In addition, patients can be left with many symptoms that impair the quality of life from a critical illness, its treatment methods, and an extended stay in the hospital. After intensive care, deterioration of cognitive function corresponding to moderate Alzheimer's disease has been described even in young and previously healthy individuals^1^.

Not all the reasons for this are known, but for example, quite common (up to 80% ) confusion or delirium during intensive care has been identified as a risk factor^1,2^ In our ongoing research project in ASSESS- shock 2 (TYH2020341), we are investigating the connection of circulatory failure with delirium and neuropsychological recovery, as well as changes in the body's microbiome during intensive care. The COVID-19 caused by the coronavirus has also caused a significant increase in the need for intensive care among working-age people. There is still no information on the adverse effects of long-term follow-up about COVID-19 pneumonitis. Still, severe respiratory failure (ARDS, acute respiratory distress syndrome) is known to occur in the long-term as shortness of breath during exertion and deterioration of cognitive performance even one or several years after hospitalization ^3,4,5^. Based on our own clinical experience and the literature accumulated with COVID-19 patients, in addition to severe respiratory failure, a considerable number of neurological complications occur in COVID-19 patients^6,7^. Delirium is prevalent and long-lasting; it is probably related to heavy long-term ventilatory therapy and the long-term use of anesthetics and opioids required. It is also possible that the coronavirus affects the central nervous system directly and increases the risk of several other neurological complications, such as convulsions, encephalitis, cerebral circulation disorders, and polyradiculitis^8,9^.

New laboratory markers are being used in research to assess brain damage. Neurofilament (light) (neurofilament light, NFL) is an intra - axonal protein that leaks out of degenerating axons. This increases the NFL concentration in the cerebrospinal fluid and blood in patients with central nervous system disease involving neuronal damage. Cerebrospinal fluid and blood concentrations correlate well with each other in different neurological disease states and with the severity of the disease. The latter has been demonstrated in neurodegenerative diseases, but also recently in acute hypoxia in ischemic damage in cardiac arrest patients^10^. The neurofilament concentration increases slowly within weeks and remains abnormal for months. NFL is currently considered the best marker of neurodegeneration because it has few confounding sources of error^10, 11^. Plasma NFL has been found to rise in connection with acute neurological damage and in the acute phase of Covid-19^12^.

ApoE lipoprotein is a lipoprotein involved in the body's fat metabolism, which is also linked to the risk of hypertension and atherosclerosis and the risk of delirium and neurodegenerative diseases such as Alzheimer's disease^13^. It has six allelic types, ApoE2, ApoE3, and ApoE4, which occur in six combinations. In the European population, about 15-20 % of the population has the ApoE4 allele, and homozygotes have a 14-fold risk of developing Alzheimer's disease. ApoE4 has been shown in vitro to be associated with easier entry of certain virus types into the cell. In a recently published study based on biobank data, it was concluded that the ApoE4 allele seemed to predispose patients to a more severe disease picture of COVID-19 when the underlying diseases associated with it were considered in the analysis^14^. The connection to neurological complications in the acute phase of COVID-19 or as late complications after a critical illness is not known. To our knowledge, there are no previous studies on the subject.

Cardiac enzymes have been reported to be elevated in approximately 12-35% of hospitalized COVID-19-patients, especially in severe disease, presumably based on infection-related myocarditis (myocarditis), ventricular overload, or ischemia^15,16^. Myocarditis can be asymptomatic or present as arrhythmias, progressive failure, and cardiogenic shock^17^. So far, there is no information on the long-term effects of COVID-19-infection on cardiovascular health, such as post-infection scars and myocardial function. Also, severe pulmonary dysfunction and the risk of pulmonary embolism can burden the right ventricle^18^. The prothrombotic tendency is increased in patients with COVID-19. Already in the early stages of the pandemic, the activation of the coagulation system was found to have a connection with mortality. In the acute phase of the disease, high D-dimer is strongly connected to an increased risk of death^19,20^. As far as we know, there is still no comprehensive research data on the recovery of the COVID-19 patient’s coagulation system in longer-term follow-up.

For ten years now, our intensive care outpatient clinic has monitored the recovery of patients, especially after long periods of intensive care, and reviewed their experiences during intensive care with patients. Based on our unpublished data, 2-3 months after intensive care, patients report still suffering from many symptoms affecting their quality of life, such as insomnia, nightmares, depression, apathy, exhaustion, and cognitive problems. Memories of delirium are common and disturbing, and going through them with patients is crucially important, and just saying them and declaring them normal helps many. Currently, the intensive care outpatient clinic is temporarily on hiatus due to the challenges brought by the information system change. COVID patients risk missing out on an essential follow-up appointment with an intensive care physician. For this reason, we now want to organize a follow-up outpatient clinic visit as a research project, where we go over issues related to intensive care and his current condition with the patient and, at the same time, investigate neurological and neuropsychological recovery related to long-term recovery from intensive care with clinical tests and imaging methods. The outpatient clinic visit also examines the healing of physical performance, the respiratory system, and immune defenses from a severe illness. It investigates heart symptoms that appeared during or after the disease.

Smells evoke strong positive and negative feelings. Thus, the loss of the sense of smell can significantly worsen the quality of life. Upper respiratory tract infection caused by a virus is the most common cause of loss of sense of smell. During the COVID-19 pandemic, changes in the sense of smell and taste have even been a primary symptom in some of those affected by the coronavirus infection (SARS-CoV-2)^21^. 32-66 % of olfactory disorders after an upper respiratory tract infection recover spontaneously^22^. Olfactory training has been shown to help the sense of smell in recovery^23^. The size of the olfactory coil has been shown to have a predictive value regarding the recovery of the sense of smell^24^. In some patients with coronavirus infection, the sense of smell has recovered within two weeks. Long-term follow-up regarding the recovery of the sense of smell is currently unknown. The study also evaluates whether the continuation of the hyperinflammatory state can be related to prolonged symptoms after COVID-19.
Matrix metalloproteinases (MMP) -7 and -9 have been described to occur in elevated concentrations in many chronic lung diseases, and recently MMP-9 was also shown to be associated with more severe COVID-19 respiratory failure^25^. MMPs are involved in modifying the intercellular space, e.g., of neutrophils endopeptidases released from granulocytes, which have multiple roles in acute and chronic inflammation. MMP-8 levels, among others, are associated with reactive arthritis and coagulation disorders^26, 27^. MMP regulation involves, among other things, proinflammatory cytokines, and at the tissue level, they are regulated by MMP tissue inhibitors, TIMPs. TIMP-1 has been described as an independent prognostic factor with 1-year mortality in patients with acute respiratory failure^28^.

**II Research questions, hypothesis, research goal**

The study aims to find out (Q=the question layout, H=hypothesis):

1) Q: Do patients treated in the intensive care unit due to the coronavirus show a decline in cognitive performance revealed in extensive neuropsychological tests compared to reference values determined from the general population?

H: Neuropsychological tests show changes in some patients compared to the general population of the same age group.

2) Q: Did any clinically observed neurological complications occur during intensive care?

H: Neurological complications such as delirium and cerebrovascular disorders occurred during intensive care.

3) Q: How have patients recovered from a severe illness neurologically?

H: Most of them have recovered well neurologically, but some may find symptoms in a detailed examination.

4) Q: Does the MRI examination show changes compared to the COVID-19 patients who survived without intensive care treated in the ward?

H: Patients with neurological abnormalities on clinical examination may have radiologically detectable changes on head MRI.

5) Q: Are the patients' neurological symptoms related to white matter damage that could be detected by determining neurofilament levels?

H: Patients with neurological or neurocognitive symptoms can be detected in plasma neurofilament levels compared to non-COVID patients and COVID patients who are neurologically asymptomatic.

6) Q: Is the ApoE4 allele more common in patients with severe Covid-19?

H: In intensive care and hospitalized Covid-19 patients, one or two ApoE4 alleles are detected more often than in patients with Covid-19 at home or controls who have not had a coronavirus infection.

7) Q: Do elevated neurofilament levels and any ApoE allele predict long-term neurological symptoms?

H: Patients with an elevated neurofilament level 6 months after the disease have more neuropsychological changes five years after the infection.

8) Q: Do the patients have a weakening sense of smell or taste compared to the average population 6sixmonths after becoming ill and are there any changes in the neural pathways of the sense of smell on MRI?

H: Some patients have changes in their sense of smell and taste, which have not recovered well or only partially after six months of illness. An MRI examination shows changes in the olfactory nerve or neural pathway.

9) Q: What are the patients' physical performance and lung function parameters 3 and 6 months, and two years after intensive care?

H: In some patients, lung function and physical performance have not recovered to the level of reference values calculated from an average population of the same age.

10) Q: What is the state of the patient’s immune system (is there long-term anergy or other leukocyte dysfunction six months after intensive care)?

H: The functioning of the immune system may still be weakened after six months of illness.

11) Q: Do those iin intensive careor inpatient unit have cardiovascular symptoms?

H: During and/or after the coronavirus infection, there are cardiac symptoms, and they have been more common and continued longer in patients treated in intensive care in demanding patients.

12) Q: Are myocarditis changes visible on magnetic resonance imaging of the heart, and are they present in connection with patients' poorer recovery and cardiac symptoms?

H: Fatigue and slow performance in some patients, especially those who needed intensive care, the background of recovery may be detectable by magnetic resonance imaging sequelae of myocarditis.

13) Q: Can changes in blood clotting factors be seen in Covid-19 infection in sick patients six months after the acute illness phase compared to clinical coagulation factor samples taken in the acute phase?

H: Blood coagulation factors have normalized six months after becoming ill.

14) the partial study investigating SARS-CoV-2 immunity aims to develop tests to measure COVID-19 immunity and bring additional information about the infection immunity and its duration. This is also important for the Covid-19 vaccine in monitoring effectiveness, as the test can be used to measure the vaccine separately induced and infection-induced immune response.

15) Q: Can elevated MMP -7, -8, or-9 concentrations or cytokines or tissue inhibitors involved in their regulation have abnormal concentrations, and whether the potentially elevated levels are associated with clinical symptoms and findings, e.g., lung function or imaging?

H: In some patients who are still severely symptomatic, there are elevated levels of inflammatory markers. The goal is to characterize the patients' long-term recovery and, if necessary, refer the patients to appropriate follow-up examinations or rehabilitation.

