**Admission criteria:**

- 18 years old

- the language of business is Finnish or Swedish. For the neuropsychological part of the study, only persons whose business language is Finnish can be included because there are no validated versions of tests for Finnish-Swedes and the test results are very language sensitive. In all other sub-investigations, persons whose business language is Swedish can also be included.

-is in intensive care in one of HUS's intensive care units due to a severe coronavirus infection

-Is involved in the RECOVID study

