**Exclusion criteria:**

-pregnancy

- a significant neurological disease diagnosed before the coronavirus infection, such as a severe one

the aftermath of a brain injury or cerebrovascular accident

-sensory impairment

- memory disorder

-Parkinson's disease

-disability

Section-specific exclusion criteria, if any, are listed in connection with the description of each study section. The assumed number of patients is around 100-150. Patients are identified after intensive care using a registered COVID-19 diagnosis from the intensive care quality database, after which they are contacted and asked to participate in the study. Patients are sent a *Patient and Next of kin Research Information Sheet* and a consent form with the contact information of the research team for further details. For the continuation of the study, new information about the subject and consent forms will be sent to the subjects by post, or their consent will be asked when meeting them at the follow-up clinic. Among the research subjects, there are only people who use Finnish as their business language, so the research documents for further research have only been prepared in Finnish.

Control patients are recruited through a newspaper advertisement and with the help of social media. Control patients are persons with a confirmed coronavirus infection whose severity of illness did not require intensive care, but the disease was contracted at home (N=50). Another control group, patients who received treatment for coronavirus infection in a hospital bed ward (N=50), will be identified to ask for consent from those who receive/are receiving an invitation to a follow-up organized by the lung disease clinic. Separate written consent to participate in the study is requested from the control persons.

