| --- | --- | --- | --- |
| Three months | Who makes | Number of patients | Controls |
| Registration of clinical data from patient records (neurological symptoms and examinations during intensive care, delirium, duration of treatment and procedures, background information) | [name] [name] [name] [name] [name] | 100-150 | 50 who were in ward treatment |
| Telephone interview: modified Rankin Scale (mRS) | [name] [name] [name] [name] [name] | 100-150 | 50 inpatients + 50 COVID patients sick at home |
| Telephone interview: Montreal Cognitive Assessment (T-MoCA) | -“- | 100-150 | 50 inpatients + 50 COVID patients who got sick at home + 50 non-COVID controls |
| Behavior Rating Inventory of Executive Function, adult version (BRIEF-A) +BRIEF Informant version ABNAS Neuropsychological questionnaire | by post | 100-150 | ,, |
| Six months | by post |  |  |
| RAND-36 | by post | 100-150 | 50 inpatients + 50 COVID patients sick at home 50 + non-COVID controls |
| MFI-20 | by post | 100-150 | ,, |
| HADS | by post | 100-150 | ,, |
| Informant Questionnaire on Cognitive Decline (IQCODE-CA) | by post | 100-150 | 50 inpatients + 50 COVID patients who got sick at home |
| Behavior Rating Inventory of Executive Function, adult version (BRIEF-A) +BRIEF Informant version | By mail (or NPS in connection with the study) | 100-150 | 50 inpatients + 50 COVID patients sick at home + 50 non-COVID controls |
| Background information | visit (see Visit 1 below) | 100-150 | ,, |
| modified Rankin Scale ( mRS) | visit | 100-150 | ,, |
| Montreal Cognitive Assessment ( MoCA ) | visit | 100-150 | ,, |
| National Institute of Health Stroke Score (NIHSS) | visit | 100-150 | ,, |
| CFS-9 ( clinical frailty scale ) | visit | 100-150 | ,, |
| Olfactory screening test | visit | 100-150 | ,, |
| Follow-up of lung diseases (with the patient's consent, data retrospectively for comparison) | Lung x-ray, spirometry, and diffusion capacity measurement, telephone interview (skin and allergy hospital) | 100-150 | Data from clinical lung function tests of 50 patients who were in ward treatment |
| **Visit 1** |  |  |  |
| Neuropsychological research [name] | Student /[name]/[name]/ [name]/ [name] | 100-150 | 50 inpatients + 50 COVID patients sick at home + 50 non-COVID controls |
| Laboratory samples (immunology) | HUSLAB | 10-50 |  |

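### Hypothesis 1 would be met by almost any healthy sample, and it leaves out the non-COVID controls who take the same neuropsychological tests

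*Protocol*

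**What the plan says.** Protocol section II, question 1, asks whether intensive care patients "show a decline in cognitive performance revealed in extensive neuropsychological tests compared to reference values determined from the general population". The hypothesis answers: "Neuropsychological tests show changes in some patients compared to the general population of the same age group". The only comparator named is the norm, and the only criterion is that some patients show changes.

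Section III describes 50 control subjects without COVID-19. They are sought among the patients' close circle so as to resemble them in education and socioeconomic status, with university staff as a fallback. The section says that the table shows the sub-studies in which these controls will be compared with the other participants. In Table 1, the neuropsychological row under Visit 1 lists ward, home and non-COVID controls, 50 each. The five-year testing row lists the same groups.

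On numbers, section III says: "The assumed number of patients is around 100-150". The admission criteria add: "For the neuropsychological part of the study, only persons whose business language is Finnish can be included".

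Question 9 asks: "What are the patients' physical performance and lung function parameters 3 and 6 months, and two years after intensive care". Its hypothesis has the same form as hypothesis 1: "In some patients, lung function and physical performance have not recovered to the level of reference values". In Table 1 the control cells are empty for the walk test and the Visit 2 spirometry. The only lung comparison data are clinical results from 50 ward patients.

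**The concern.** A reference value is a point in the distribution of healthy people, so a known share of them lies below it. An extensive battery gives each person several chances of a low score. A hypothesis satisfied by changes in some patients is therefore satisfied by people with no illness effect at all.

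If the result is reported as worded, a confirmed hypothesis 1 could be read as evidence that critical COVID-19 harms cognition when it shows only that norms have a lower tail. Differences between patients and the norm sample that predate the illness could contribute as well. The protocol plans a comparator that would help with both problems, but the hypothesis does not name it. Hypotheses 5 and 6 do name people without COVID-19 as comparators, so the omission is particular to this question.

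**Working it through.** The protocol gives no alpha, power, cut-off or derived sample size for question 1, so there is no figure to reproduce.

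**Inputs from the protocol.** 100 to 150 intensive care patients; 50 non-COVID controls; at least 30 MRI patients who must also be in the neuropsychological part (section III, Imaging).

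**Assumptions.** Normally distributed scores; cut-offs from -1.5 SD to the 1st percentile; 8 to 20 scores per person; inter-score correlation 0 to 0.5; two-sided alpha 0.05. Hypothesis 1 is read as met when at least one patient is below the cut-off, since the text sets no higher bar.

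**Step 1: one test, everyone healthy.** With tail probability p, P(at least one below) = 1 - (1 - p)^n.

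| Cut-off | n = 30 | n = 50 | n = 100 | n = 150 |
|---|---|---|---|---|
| -1.5 SD (p = 0.0668) | 87.4% | 96.8% | 99.9% | >99.99% |
| 5th percentile | 78.5% | 92.3% | 99.4% | 99.95% |
| -2 SD (p = 0.0228) | 49.9% | 68.4% | 90.0% | 96.8% |
| 1st percentile | 26.0% | 39.5% | 63.4% | 77.9% |

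At the 5th percentile the expected number below is 100 × 0.05 = 5 to 150 × 0.05 = 7.5. Requiring at least two people instead of one still gives 96.3% and 99.6% at that cut-off.

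**Step 2: a battery, everyone healthy.** With k independent scores, a healthy person has at least one low score with probability 1 - (1 - p)^k. With correlation, that expression is averaged over a shared normal factor.

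- At -1.5 SD, 27% (8 scores, correlation 0.5) to 75% (20 scores, correlation 0) of healthy people have at least one low score. About 10% to 39% have two or more.
- At -2 SD, the least favourable case is 8 scores with correlation 0.5: 11.6% have at least one. With n = 30, 1 - (1 - 0.116)^30 = 97.5%.
- With 10 scores and correlation 0.5 the share is 13.3%, and n = 30 gives 98.6%.

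**Step 3: comparison with the controls.** SE = sqrt(1/n + 1/50) in SD units. The difference detectable with 80% power is (1.960 + 0.842) × SE. Power for 0.5 SD is Φ(0.5/SE - 1.960).

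| Patients vs 50 controls | SE | Detectable difference | Power for 0.5 SD |
|---|---|---|---|
| 150 | 0.163 | 0.457 SD | 86.5% |
| 100 | 0.173 | 0.485 SD | 82.3% |
| 50 | 0.200 | 0.560 SD | 70.5% |
| 30 | 0.231 | 0.647 SD | 58.1% |

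For impairment proportions of 30% against 10% (assumed), power is 82% with 100 patients and 86% with 150. If the control rate is 15% instead, it falls to 52% and 56%. With no true difference, such a test would be positive about 5% of the time, against the near certainty in step 2.

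**The case against.** The strongest reply is that the controls are not wasted. Section III says they will be compared with the other participants, and Table 1 puts them in the neuropsychological row. That stands. The fault lies in the wording of question 1 and its hypothesis, and the study as a whole is not left without evidence. An analysis plan that is not shown may also define impairment. However, that would not change the comparator and criterion which the protocol itself names.

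A reader might infer that hypothesis 1 cannot fail. The document does not support that. It states no decision rule, and with one test, a strict cut-off and a small sample the hypothesis could fail (49.9% at n = 30 and -2 SD). With an extensive battery, failure is merely very unlikely.

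A reader might also infer that the norms are matched on age alone and ignore education. The protocol mentions the age group but does not say how the norms are otherwise stratified, so this is conjecture.

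Nor would the controls reveal decline within a person. Table 1 has no testing before the illness, and the controls cannot supply it. The exclusion of prior memory disorder and significant neurological disease, and the informant questionnaire, address this only in part.

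For question 9, it would be wrong to say that a tested non-COVID control group is left unused, because none exists. That question is also descriptive.

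**Conclusion.** The point holds for hypothesis 1 as worded. A healthy sample given an extensive battery would satisfy it with at least 97.5% probability across the assumed range of 8 to 20 scores, correlation 0 to 0.5 and cut-offs of -1.5 to -2 SD, even at n = 30. Confirming it therefore carries little information about an effect of COVID-19 or intensive care. A better comparator with the same testing is already planned.

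The size rests on assumed cut-offs, battery length and correlation, and on reading the criterion as at least one patient. Hypothesis 9 shares the wording and is a secondary point.

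Severity is moderate. A reader might rank the point higher because the question is listed first, but the protocol poses 15 parallel questions without naming a primary one, and no sample size or decision depends on this sentence.

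**What to change.** Restate hypothesis 1 as a difference between intensive care patients and the concurrent non-COVID controls, in two measures: the mean composite z-score, and the proportion meeting one impairment rule fixed in advance (for example, at least two scores below -1.5 SD). Adjust both for age, sex and education. Use reference values only to scale the scores, and let the controls supply the rate at which healthy people meet the rule. Report the result as a group difference and drop the word decline.

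For hypothesis 9, report the mean z-score against 0 and the proportion below the lower limit of normal against the rate expected in the reference population.

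The cost is rewording two hypotheses and their analysis; no new visits, tests or participants are needed. The hypotheses become harder to confirm. Power for question 1 depends on how many Finnish-speaking patients are tested: about 82% to 87% for 0.5 SD at 100 to 150 patients, about 71% at 50. State that number beside the hypothesis.
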